#### Follow-up assessment

All the included patients will be recalled for clinical and radiographic assessment at 12, 24, 36, and 60 months after crown placement. Survival rates, complication rates and marginal bone level will be recorded. Implant survival rates are defined as the percentage of implants still retained in the mouth. Implant success is defined according to Cochran et al. 2002 [17]. Both biological and mechanical complications will be recorded. Periapical radiographs will be taken immediately after implant surgery, and at the 1-year, 3-year, and 5-year examination. For standardization, a paralleling technique with a Rinn film holder (XCP Instruments; Rinn Corporation, Elgin, IL, USA) will be conducted. Radiographic analysis will be conducted by a software program (SIDEXIS 1.12; Sirona Dental Systems GmbH, Bensheim, Germany). Biological complications refer to peri-implant mucositis (bleeding on probing positive, and without surrounding bone loss) and peri-implantitis (bleeding on probing positive, probe pocket depth ≥5 mm and with surrounding bone loss), and technical complications are veneer ceramic chipping, framework fracture, loss of retention, screw loosening, abutment and implant fracture.

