### Outcomes

#### Baseline assessment

Resonance frequency analysis (RFA) measurements, treatment time and patient-reported outcome will be recorded. RFA assessment will be performed immediately after surgery, 2 weeks later and 3 months after surgery. RFA measurements will be conducted by the Osstell™ mentor (Integration Diagnostics AB, Göteborg, Sweden). Treatment time will be calculated from incision beginning to suture finishing. Patients will be asked to give their answers regarding intraoperative discomfort and postoperative pain immediately and two weeks after surgery using a 100-mm visual analogue scale (VAS) with word descriptors "very dissatisfied" to "very satisfied" on the left and right respectively.

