#### Sample size

The primary outcome is the implant survival rate. The criterion for significance is set at α = 0.05 (type I error) and at β = 0.10 (type II error). The analysis is two-tailed. The survival rate reported by Esposito et al. 2014 (92 % in the longer group and 85.7 % in the short group) is used to estimate the sample size [15]. Forty-two cases per group can result in a power of 80 %. Assuming the dropout rate at 20 %, 50 cases per group and 150 cases in total are finally determined.

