#### Statistical analysis

Generalized estimating equations will be used to manage the correlated relationships between multiple implants in the same patient. The data of different patients are assumed to be independent. Each patient will be assigned a number, which will be an indicator (X) for primary and secondary outcome (Y). For the patient (i) and implants (j), mean model is logit(E(Yij|Xij)) = beta0 + beta1*I(Xij = 2) + beta2*I(Xij = 3), and variance model is Var(Yij|Xij) = E(Yij|Xij)*(1-E(Yij|Xij)). For patient-reported outcome (VAS), ANOVA will be used to assess the difference among the three groups. The level of significance is set at 0.05.

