#### Missing data

Sample size calculation was performed accounting for possible loss to follow-up. Moreover, we will account for the data not missing at random due to unbalanced loss to follow-up by handling drop-outs as nonsuccess or nonsurvival using the intention-to-treat principle.

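### Counting every drop-out as a lost implant lets loss to follow-up dominate the primary outcome, whose visit and denominator are also left open

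*Protocol article*

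**What the plan says.** - **Primary outcome** (Sample size): "The primary outcome is the implant survival rate". No time point is attached.
- **Definition** (Follow-up assessment): "Implant survival rates are defined as the percentage of implants still retained in the mouth". It does not say whether the percentage is of implants placed or of implants that received a crown.
- **Visits** (Follow-up assessment): "All the included patients will be recalled for clinical and radiographic assessment at 12, 24, 36, and 60 months after crown placement". What they capture is also stated: "Survival rates, complication rates and marginal bone level will be recorded".
- **Contacts before the crown** (Baseline assessment): "RFA assessment will be performed immediately after surgery, 2 weeks later and 3 months after surgery". The Surgical procedures section adds an impression after 3 to 4 months of healing. Survival is not listed among the items recorded at these contacts.
- **Model** (Statistical analysis): a logistic GEE with indices for patient and implant and two treatment indicators. It has no term for visit or time.
- **Drop-outs** (Missing data): the article expects that losses may be unequal between arms and related to outcome. It answers this by "handling drop-outs as nonsuccess or nonsurvival using the intention-to-treat principle". No other rule is given, so this one governs the primary outcome.
- **Planning figures** (Sample size): 92 % against 85.7 %, two-sided 5 %, 42 per group for 80 % power, and 20 % drop-out, giving 50 per group.

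**The concern.** True implant loss is planned at 8 to 14 %, while drop-out is planned at 20 %. Once a drop-out counts as a lost implant, the outcome mainly measures attendance. This has two consequences. With equal drop-out, the true difference shrinks and the variance grows, so power falls. With unequal drop-out, a difference appears between arms whose implants do equally well. Unequal drop-out is the very situation that the rule is meant to handle.

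The second matter is what the single primary result is. Four visits can each yield a survival percentage, and the model as written applies equally to any of them. The Background says that the earlier trials, one of which supplies the planning rates, reported at 1 year, whereas this trial runs for 5 years. Either end of the schedule could therefore be defended after the data are seen. With no denominator stated, it is also open whether an implant lost during healing counts.

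**Working it through.** **Assumptions throughout.** One implant per patient, two-arm comparison at two-sided 5 %, drop-out unrelated to true implant loss.

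**Formula.** Power = Φ[(|d| − 1.96·SE₀)/SE₁] plus the small opposite tail, with SE₀ = √(2p̄(1−p̄)/n) and SE₁ = √([p₁(1−p₁)+p₂(1−p₂)]/n).

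**1. The plan's own figure.** At 92 % against 85.7 % and n = 42, power is about 15 %, not 80 %. A two-sided test with 80 % power needs 391 per group. The stated 50 matches 42 × 1.2 = 50.4, whereas 42/0.8 gives 53. That shortfall is a separate defect; it is shown here only because it sets the baseline.

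**2. Equal drop-out of 20 %, counted as failure.**
- Observed survival: 0.8 × 0.92 = 0.736 and 0.8 × 0.857 = 0.686.
- The difference shrinks from 6.3 to 0.8 × 6.3 = 5.0 points.
- The binomial variance p̄(1−p̄) rises from 0.8885 × 0.1115 = 0.099 to 0.711 × 0.289 = 0.206.
- Share of counted failures that are drop-outs: 0.20/0.264 = 76 % in the longer-implant arm and 0.20/0.314 = 64 % in the short-implant arm.
- Power at n = 50: SE₀ = 0.0907, SE₁ = 0.0905, and (0.0504 − 0.1777)/0.0905 = −1.41, giving 0.080. With the opposite tail (0.006) it is 0.086.
- Without the rule: 0.142 if only 40 per arm are evaluable, and 0.168 if all 50 are followed.

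The Sample size section enlarges n as though drop-outs left the analysis, while the Missing data section keeps them in as failures.

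**3. Unequal drop-out, no true difference (92 % in both arms).** The article gives only 20 % overall, so the split is assumed. The false difference is 0.92 × (gap in drop-out).

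| Drop-out | Observed survival | False difference | Chance of p < 0.05 (n = 50) |
|---|---|---|---|
| 20 % vs 20 % | 73.6 % vs 73.6 % | 0 | about 5 % |
| 17.5 % vs 22.5 % | 75.9 % vs 71.3 % | 4.6 points | about 8 % |
| 15 % vs 25 % | 78.2 % vs 69.0 % | 9.2 points | about 18 % |

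For the last row, (0.092 − 0.1728)/0.0877 = −0.92, giving 0.178; exact binomial calculation gives 0.182. With 92 % in both arms and no drop-out, the exact rate is 0.047.

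**4. Free choice among four visits.** This was simulated under no difference, 50 per arm, one pair, with chi-square tests at 12, 24, 36 and 60 months on the same implants. With exponential loss and 60-month survival of 90 %, at least one p < 0.05 occurs in about 10.6 % of trials. With 60-month survival of 73.6 %, it is about 13.9 %. At 60 months alone it is about 5 %. A three-group test under other assumed loss paths gives 10 to 13 %. Four independent tests would give 1 − 0.95⁴ = 18.5 %, which overstates the effect because the visits are nested.

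**The case against.** **The drop-out rule is deliberate.** The article gives a reason for it: losses may be informative and unequal. A reader might infer that the crude percentage forced the rule, but the document does not say so. Censoring assumes the opposite, uninformative loss, so replacing one with the other is not free. This stands as a reason to keep the rule as a sensitivity analysis. It does not rescue it as the primary one, because treating every drop-out as a loss is not neutral between arms when drop-out differs.

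**Power is poor either way.** This is true: 14 to 17 % is also useless, and the main cause is the sample size. The rule makes it worse but is not the root of it.

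**The time point may be in an analysis plan not shown.** This is fair. The 5-year study length makes 60 months the natural reading, and on its own this part is close to missing detail. The 10 to 14 % error arises only if someone picks the best visit. A reader might infer that four tests are planned; nothing in the article plans them. Nor should the figure be multiplied up over the three pairs of arms: unadjusted testing of all pairs at 60 months alone already gives about 12 %, which naming a visit would not cure.

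**Early losses.** A reader might infer that implants lost before the crown would go unseen. The article does not support this. Patients are seen at 2 weeks, at 3 months and at the impression, and all included patients are recalled, not only those with crowns. The visit schedule runs from the crown, but the survival definition states no clock. The reference to intention-to-treat points towards counting early losses, without saying so. What remains is an unstated denominator.

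**Conclusion.** The concern holds for the drop-out rule and, with less weight, for the undefined time point and denominator. Followed as written with 20 % drop-out, the rule would make 64 to 76 % of counted failures drop-outs and cut power at 50 per arm to about 9 %. Those figures rest on the plan's own rates, one implant per patient, and drop-out independent of implant loss. The 9.2-point false difference and 18 % rejection rest on an assumed 15 % against 25 % split; a 5-point gap would give about 8 %. The 10 to 14 % error from choosing among visits is conditional on that choice being made and on assumed loss paths. It shows what is at stake and is not an error rate of the plan as written.

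**What to change.** 1. Count every implant placed, with one clock starting at placement, so that losses during healing are included.
2. Name one primary time point, for example the 5-year examination, and express it on that same clock, since the visit itself is scheduled from the crown. Make the other visits descriptive.
3. Analyse time to implant loss using each patient's follow-up to the last visit, with clustering on patient. Either a Kaplan-Meier estimate with robust variance or a discrete-time version of the planned GEE would serve. The discrete form suits losses that are found only at visits. A Cox model is not essential: the planning rates imply only 50 × 0.08 = 4 to 50 × 0.143 = 7 losses per arm.
4. Keep drop-out counted as failure as a worst-case sensitivity analysis, and report drop-out by arm.

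**Cost.** Changes to the analysis wording, plus recording the date of loss, or the visit interval in which it was found. The downside is that censoring assumes uninformative loss, which item 4 probes. None of this repairs the sample size, which needs its own correction.

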## Abstract

**Background:**

Nowadays, short dental implants are being increasingly applied in extremely resorbed posterior regions. The recent studies have indicated that short implants present a similar success rate to conventional implants. It is assumed that short implants can avoid additional surgical morbidity and are less technically demanding. However, high-quality evidence (≥Ib: evidence from at least one randomized controlled trial) on comparing the clinical outcome of short implants and longer implants combined with osteotome sinus floor elevation (OSFE) technique is limited.

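### The secondary complication outcome lists no surgical or sinus event, leaves one type of bleeding implant in neither biological class, and rests on conflicting radiograph schedules at 24 months

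*Protocol article*

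**What the plan says.** The section Follow-up assessment of the protocol article states: "Both biological and mechanical complications will be recorded". It then says what each kind is. For the first kind it gives two diseases. The milder one is worded: "Biological complications refer to peri-implant mucositis (bleeding on probing positive, and without surrounding bone loss"). The more severe one adds a condition on pocket depth and reverses the one on bone: "peri-implantitis (bleeding on probing positive, probe pocket depth ≥5 mm and with surrounding bone loss"). For the second kind it gives a list: "technical complications are veneer ceramic chipping, framework fracture, loss of retention, screw loosening, abutment and implant fracture". Complication rates are recorded at the recalls, where patients are "recalled for clinical and radiographic assessment at 12, 24, 36, and 60 months after crown placement". The film schedule in the same section reads: "Periapical radiographs will be taken immediately after implant surgery, and at the 1-year, 3-year, and 5-year examination".

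Around surgery, the section Baseline assessment says: "Resonance frequency analysis (RFA) measurements, treatment time and patient-reported outcome will be recorded". Complications are not on that list.

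On rationale, the Abstract says: "It is assumed that short implants can avoid additional surgical morbidity and are less technically demanding". The Background section adds that the extra procedure may raise morbidity after surgery as well as cost. Under Allocation and blinding, only groups 2 and 3 are assigned OSFE. Under Sample size, implant survival is the primary outcome, so complications are secondary.

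**The concern.** The trial compares placing a short implant alone with placing a longer one after lifting the sinus floor. The expected price of the lift is surgical morbidity, and complications are a declared outcome. A reader of the results will look to the complication comparison for that price, but the listed events arise around the implant and its crown.

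The biological definitions raise a separate problem. If they are not exhaustive among bleeding implants, the count need not rise as an implant gets worse. Marginal bone level is itself compared between arms and may differ between them. An arm that loses more bone could then show fewer biological complications.

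Finally, if bone-loss status is not available at one recall, the disease classes at that visit are not comparable with those at the others.

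**Working it through.** The article gives no figure to reproduce here, so the check is one of definitions and schedule.

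**Step 1: surgical events.** I take the article's mechanical and technical complications to be the same class.

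- Biological class: mucositis and peri-implantitis.
- Technical class: six prosthetic or implant failures.
- Peri-surgical record: resonance frequency analysis (RFA), treatment time, visual analogue scale (VAS).

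None of the three contains an intraoperative, early postoperative or sinus event. Sinus membrane perforation and postoperative sinusitis would be examples; they are mine, as the article names neither.

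Timing points the same way. The impression follows 3–4 months of healing (Surgical procedures) and the first recall is 12 months after the crown. The first scheduled complication assessment is therefore at least 3 + 12 = 15 months after surgery. Events not written down at the time may not be recoverable then.

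**Step 2: the biological classes.** Write B for bleeding, L for bone loss, P for a pocket of at least 5 mm.

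- Mucositis = B and not L
- Peri-implantitis = B and L and P

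The four bleeding-positive combinations are:

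| Bone loss | Pocket ≥5 mm | Class |
|---|---|---|
| No | No | Mucositis |
| No | Yes | Mucositis |
| Yes | No | Neither |
| Yes | Yes | Peri-implantitis |

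Two are mucositis, one is peri-implantitis and one is unclassified. Take a bleeding implant with a 4 mm pocket. With no bone loss it is mucositis and is counted. If it then loses bone while the pocket stays at 4 mm, it meets neither definition. The definition states no minimum amount of bone loss, so any recorded loss could move an implant into the gap.

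**Step 3: month 24.**

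- Recalls described as clinical and radiographic: {12, 24, 36, 60} months.
- Recalls with a scheduled periapical film: {12, 36, 60} months.
- Difference: {24}, that is, one recall of four.

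The two sentences disagree on that visit. L appears in both biological definitions, as a required absence in one and a required presence in the other. If the film schedule governs, no scheduled periapical film supports either class at 24 months.

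**The case against.** The strongest reply is that the surgical burden is measured elsewhere. The Abstract and Discussion expect short implants to save operating time, complexity and discomfort after surgery. Treatment time and the VAS for discomfort and pain, taken immediately and at two weeks, address two of these. This stands, and it rules out a stronger reading that a reader might infer: that the trial misstates the trade-off it exists to test. What it does not supply is events. Treatment time is not a harm, the VAS is anchored on satisfaction rather than pain, and neither identifies a surgical or sinus complication.

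A second reply is that a condensed article may leave operative and adverse-event forms to the full protocol, and that the Abstract and Objective list complications without restriction. No sentence says that surgical events will go unrecorded. This is fair, but the article does not merely stay silent. It says what the biological and technical complications are, and it lists what is recorded around surgery.

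Three other stronger readings also fail:

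- A reader might infer that all surgical complications are left out in two of the three arms, or that sinus harms can arise only from OSFE. All three arms have flap surgery and implant placement, and a 6 mm implant may be placed where bone height is 6 mm. The document does not confine sinus involvement to groups 2 and 3.
- A reader might infer that gap implants are counted as healthy. The article does not say how they are counted; they are unclassified. Their bone loss is not lost to the trial, because marginal bone level is recorded separately.
- A reader might infer that complications cannot be classified at 24 months. The article promises radiographic assessment then, so this is a contradiction and not a proven impossibility. Technical complications, as listed, do not depend on bone level.

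**Conclusion.** The concern holds on three points, all within a secondary outcome.

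1. The complication lists contain no surgical or sinus event. If OSFE does add such events, as the article itself supposes, the complication comparison would tend to understate the surgical cost of OSFE.
2. One of the four bleeding-positive combinations belongs to neither biological class. This follows from the definitions alone. If only implants meeting a stated definition are counted, an implant can leave the count as it worsens.
3. Two sentences of one section conflict on radiographs at 24 months, one of the four recalls, and both biological classes depend on the answer.

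The article gives no frequency for surgical events, for bone loss with shallow pockets, or for disease at 24 months. The effect on any complication rate therefore cannot be computed, and the bias between arms in point 2 is possible but not shown. The primary survival analysis is not affected.

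**What to change.** - **Surgical events.** Add a surgical/sinus complication class, with its events listed in advance, recorded in all three arms at surgery and at the existing two-week assessment, and compared by arm. The cost is about one case-report-form page at contacts that already take place. The small downside is that the operator who records events at surgery knows the assignment.
- **Biological classes.** Add a separate category for bleeding with bone loss and pocket depth under 5 mm, and count it in the biological complication rate. Relabelling these implants as mucositis would contradict the article's own requirement that mucositis has no bone loss. The cost is wording only.
- **Month 24.** Reconcile the two radiograph sentences. If no film is taken at that visit, report only bleeding, pocket depth and technical complications there, and leave the visit out of bone-level and disease-class rates. If a film is taken, add the visit to the film schedule. The first resolution costs wording only; the second means that a film is taken at that recall, as the first of the two sentences already implies.

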#### Sample size

The primary outcome is the implant survival rate. The criterion for significance is set at α = 0.05 (type I error) and at β = 0.10 (type II error). The analysis is two-tailed. The survival rate reported by Esposito et al. 2014 (92 % in the longer group and 85.7 % in the short group) is used to estimate the sample size [15]. Forty-two cases per group can result in a power of 80 %. Assuming the dropout rate at 20 %, 50 cases per group and 150 cases in total are finally determined.

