To our knowledge, three randomized controlled clinical trials compared short implants versus longer implants in combination with OSFE procedures in the posterior maxilla [13–15]. Similar survival rates were reported in short and longer implant groups after a 1-year follow-up. However, the limited sample size (101 patients in Thoma et al. 2015 [14], 41 patients in Gujie et al. 2014 [13] and 30 patients in Esposito et al. 2014 [15]) might lead to insufficient statistical power. In addition, the lateral sinus floor elevation technique was performed in those patients with RBH from 5 to 8 mm, while the OSFE technique might be more suitable from cost-effectiveness considerations. Thus, there is still an urgent need for randomized controlled clinical trials with long-term data and a sufficient sample size to provide more clinical evidence to decide the best treatment options.

Based on these, we are now designing a randomized controlled trial study with a 5-year follow-up trying to answer the research question: which is the best treatment option in atrophic maxilla with RBH from 6 to 8 mm: short 6-mm implants alone or short 8-mm implants combined with OSFE or standard 10-mm implants combined with OSFE?

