## Discussion

Implant treatment in the posterior maxilla is commonly faced with great challenges due to the limited residual bone height and poor bone quality. In 2013, our study demonstrated that high survival rates can be achieved after 5–10years for Straumann SLA Standard Plus short implants (6 or 8 mm) in the posterior region, without severe marginal bone loss and complications [18]. This result shows that Straumann short 6-mm implants are predictable and reliable in the posterior maxilla. In addition, our previous studies have also indicated that the OSFE technique is also predictable and reliable in the posterior maxilla [16, 19]. Therefore, our research group is very interested in the long-term treatment outcome of short implants alone and longer implants combined with OSFE.

The results of the trial will support better decision-making for dental implant treatment in atrophic maxillary ridges. If favorable, the use of the short implant may avoid adjunct procedures used for implant insertion, thus reducing operative time, complexity and postoperative discomfort.

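### The stated 80 % power does not follow from the plan's own inputs: 42 cases per group give about 15 % for 92 % versus 85.7 % survival, and β = 0.10 contradicts the 80 %

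*Protocol article*

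**What the plan says.** In the protocol article, under Sample size:

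- "The primary outcome is the implant survival rate".
- "The criterion for significance is set at α = 0.05 (type I error"), and "The analysis is two-tailed".
- The type II error is set "at β = 0.10 (type II error").
- The planning rates, taken from an earlier randomized trial, are 92 % survival with longer implants and 85.7 % with short ones.
- "Forty-two cases per group can result in a power of" 80 %.
- With 20 % dropout assumed, the size becomes 50 per group and 150 in total.

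Three other places bear on the figure. The Overview under Method/Design plans 225 patients, while the Abstract agrees with 150. Statistical analysis uses a GEE logit model because a patient may carry several implants. Missing data counts drop-outs as nonsuccess or nonsurvival under intention to treat. No non-inferiority or equivalence margin is given.

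**The concern.** A difference of 6.3 percentage points between two high proportions normally needs several hundred patients per arm, so 42 per arm for 80 % power looks wrong at sight. The same paragraph also sets β = 0.10, which is 90 % power, and then claims 80 %.

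The Background argues that the limited size of earlier trials "might lead to insufficient statistical power" and calls for a sufficient sample size. A reader who trusts the 80 % would take a non-significant survival result as reasonably strong evidence against a 6.3-point loss. If the true power is a fraction of that, such a result carries little information on the primary outcome.

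**Working it through.** **Inputs, all from the article.** p1 = 0.92, p2 = 0.857, two-sided α = 0.05 (z = 1.960), n = 42 per group. The comparison is pairwise with equal arms. One implant per patient is assumed, because the article gives no number of implants per patient.

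**1. The plan's own figure.** Pooled normal approximation:

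Power = Φ[(d − 1.960·SE0)/SE1], with SE0 = √(2·p̄(1−p̄)/n) and SE1 = √((p1(1−p1)+p2(1−p2))/n).

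- d = 0.063 and p̄ = 0.8885
- SE0 = √(2 × 0.8885 × 0.1115/42) = 0.0687
- SE1 = √((0.0736 + 0.1226)/42) = 0.0683
- (0.063 − 1.960 × 0.0687)/0.0683 = −1.048, so power = Φ(−1.048) = **14.7 %**

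The stated 80 % is not reproduced. The choice of formula hardly matters:

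| Variant at 42 per group | Power |
|---|---|
| Unpooled variance | 15.0 % |
| Arcsine | 15.1 % |
| Exact enumeration of the z-test | 16.2 % |
| Fisher's exact test | 8.1 % |
| Three-arm test, 2 df | 12–15 %, depending on the middle arm |
| Two arms pooled (42 vs 84) | 15–21 % |
| One-sided 0.05 (contradicts two-tailed) | 23.2 % |

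**2. Number needed.** n = [1.960·√(2p̄(1−p̄)) + zβ·√(p1(1−p1)+p2(1−p2))]²/d²:

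- 80 % power (zβ = 0.842): 391 per group
- 90 % power (zβ = 1.282), as β = 0.10 requires: 523 per group

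The ratio 391/42 is about 9.

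**3. Other group sizes in the article.** The same formula gives 16.8 % at 50 per group and 23.0 % at 75 per group (225/3). Also, 50 less 20 % leaves 40 evaluable, not 42; this changes little.

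**4. With drop-outs counted as nonsurvival.** Assume 20 % drop-out in each arm, unrelated to implant fate. The rates become 0.92 × 0.8 = 0.736 and 0.857 × 0.8 = 0.6856, and the difference shrinks to 5.0 points.

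- 50 per group: SE0 = 0.0907, SE1 = 0.0905, power = Φ(−1.406) = **8.0 %**
- 75 per group: SE0 = 0.0740, SE1 = 0.0739, power = Φ(−1.281) = **10.0 %**

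**5. What 42 evaluable per group can do.** With 92 % in one arm, the formula in step 1 reaches 80 % only when the other arm falls to about 68 %, a difference of about 24 points.

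**6. Precision.** Half-width of the 95 % confidence interval for the difference = 1.960 × SE1:

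- 42 per group: 1.960 × 0.0683 = 13.4 points
- 50 per group, no drop-outs: 1.960 × √(0.1962/50) = 12.3 points
- 50 per group, 20 % drop-outs as failures: 1.960 × 0.0905 = 17.7 points

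**The case against.** **Several implants per patient.** The GEE analysis is by implant, so the effective number could exceed 42. If implants within a patient were fully independent, two per patient would give about 25 % power and three about 35 %. About nine would be needed to approach 80 % (79 %). The plan itself treats implants in one patient as correlated, which lowers these figures. The point stands as a reason to state the assumption, not as a rescue.

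**A non-inferiority calculation behind the figure.** With an assumed 15-point margin, 92 % in both arms and one-sided 0.05, one obtains 41 per group. But the article states no margin, uses unequal rates and says two-tailed.

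**An article condenses its protocol.** That would excuse an omission. Here inputs and result are printed together, and the result does not follow.

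**Stronger readings that the documents do not support.**

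- A reader might infer that this trial has the same number per arm as the largest earlier one. The Background gives only total patients (101, 41 and 30), not arms or arm sizes, and this trial's own size is stated as both 150 and 225.
- A reader might infer that a null survival result will be read as favourable to short implants. The Discussion says "If favorable, the use of the short implant may avoid adjunct procedures used for implant insertion", but it does not define favourable, and the outcomes also include complications, bone level, treatment time and patient-reported pain. No passage equates p > 0.05 with similarity.
- A reader might turn 14.7 % into a non-significant result about 85 % of the time. That assumes one implant per patient, a single pairwise test and no drop-outs counted as failures, so it is not a forecast for this trial.

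**Conclusion.** The power statement is wrong on its own inputs, by about 65 points (80 % against about 15 %), and the number needed for 80 % is about nine times the number stated. The β of 0.10 and the 80 % contradict each other. No reading of the stated inputs, and neither enrolment figure, brings power near 80 %: it is 17 % at 50 per group and 23 % at 75, or about 8 % and 10 % under the plan's drop-out rule with 20 % lost from each arm.

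The exact percentages rest on a pairwise comparison, one implant per patient and, for the last two, equal drop-out unrelated to outcome. The conclusion does not depend on those choices. It follows that, if the assumed 6.3-point difference is true, a non-significant survival result would say little about similarity. The calculation covers survival only and says nothing about power for VAS or treatment time.

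**What to change.** 1. Reconcile 150 patients (Abstract, Sample size) with 225 (Overview); any restated power depends on this number.
2. Keep one power target: either β = 0.10 or 80 %.
3. Replace the 80 % statement with the power that the final number gives for 92 % versus 85.7 %, computed with drop-outs as nonsurvival and with the assumption on implants per patient written out. For orientation: about 15 % at 42 evaluable per group, and about 8 % at 50 per group with 20 % drop-outs counted as failures. Add the difference detectable at 80 % power, about 24 points at 42 evaluable.
4. Report pairwise survival differences with 95 % confidence intervals, and give the expected half-width: about 12–13 points without drop-outs as failures, about 18 points with them at 50 per group.
5. State that p > 0.05 is not evidence of equal survival.

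This changes wording and reporting only. No extra patients are needed; the cost is a much less favourable stated power.
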